## **19. Precautions/Minimization of Risks**

- a. Describe precautions that will be taken to avoid risks and the means for monitoring to detect risks.

The risks associated with the proposed study are minimal since moderate amounts of physical activity and a healthy diet generally promote good health, not endanger it. However, there are participants for whom such a tact is contraindicated. Our eligibility criteria are specifically established to exclude individuals for whom unsupervised physical activity and home gardening is not appropriate. We also will screen subjects directly using a mailed screener. Thus, using this multi-gated approach, we should be able to effectively screen-out any individuals for whom this intervention is contraindicated. We also will provide articles on gardening safety and health, e.g., protecting knees and back, sun protection, etc. in the study notebook that is delivered to participants prior to starting the intervention (the study notebook is an information source on gardening, health precautions and vegetable preparation).

A private Facebook group will be created to allow interested cancer survivors and Master Gardeners enrolled in the study to obtain and/or share gardening related information, such as the status of their garden (e.g., pictures, what works well, what isn't working), problems they've encountered, solutions to problems, and different ways (e.g., recipes) to enjoy the produce from the garden. Participation in this forum is optional; the opportunity to interact with their fellow study participant-gardeners is being offered per the suggestion of the mini-pilot study participants. UAB study staff and Master Gardeners will not be posting pictures of participants or their gardens to this Facebook page in order to maintain confidentiality. Participants may choose to post pictures themselves. The constructed Facebook page also will include a listing of warning signs with instructions should injury or other health problems occur. A phone number will be provided in order to communicate these with study staff.

All health occurrences will be recorded and regularly reviewed by the study staff. Any serious adverse events will be immediately communicated to [name], who will confer with her co-Investigators (especially clinician-scientist, [name] [name]) – a procedure that has worked successfully in the past. All data will be used for research purposes and will be protected and kept strictly confidential. All patients will be asked if and when they suffered adverse events during bi-monthly telephone contact with study staff and will be encouraged to report an event at any time during follow-up. Thus, at any given time, patients will have varying follow-up times. In practice, study participants will be encouraged to call-in on a toll-free number to report any adverse events that would preclude their participation in the study. Data from

these phone calls will be included in the analyses along with data generated by the follow-up surveys (checking for any duplicates and cleaning the data as necessary). Within each arm, we assume independence of events.

**If study involves drugs or devices skip Items 19.b. and 19.c., go to Item 20, and complete the Drug or Device Review Sheet, as applicable.**

- b. If hazards to an individual participant occur, describe (i) the criteria that will be used to decide whether that participant should be removed from the study; (ii) the procedure for removing such participants when necessary to protect their rights and welfare; and (iii) any special procedures, precautions, or follow-up that will be used to ensure the safety of other currently enrolled participants.

**The project manager will record all reported events in the adverse event log (including the subject's name, date, and event description). The project manager will inform the principal investigator, [name], immediately of any unanticipated study deaths or serious events that potentially jeopardize participation in the study. [name] will consult with [name] [name] on the action that should be taken. This communication will occur within 24 hours for an unanticipated study death, and within 5 business days for an unanticipated serious event. If deemed necessary, participants will be removed from the study to ensure their safety. A serious event is defined as "any event or condition that is life threatening, results in overnight hospitalization, cancer or a physical or cardiac event serious enough to require medical attention". A brief listing follows:**

- Fatal
  - Life threatening
  - Permanently disabling
  - Required or prolonged (overnight) hospitalization (Admission—not ER visit)
  - Overdose
  - Significant hazard to patient
- c. If hazards occur that might make the risks of participation outweigh the benefits for all participants, describe (i) the criteria that will be used to stop or end the entire study and (ii) any special procedures, precautions, or follow-up that will be used to ensure the safety of currently enrolled participants.

**If multiple serious adverse events occur, [name] will consult with [name] [name] on the action that should be taken in terms of continuing the study. If necessary, participants will be informed of the adverse events (via mail or phone) and given the option of continuing the study.**

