#### **15. Participants (Screening and Selection)**

a. How many participants are to be enrolled at UAB? **426 older cancer survivors**  
If multi-center study, total number at all centers: \_\_\_\_\_

b. Describe the characteristics of anticipated or planned participants.  
Sex: **Male and Female**

Race/Ethnicity: **Our sample will represent the state population for race-ethnicity (27% minority).**

Age: **65 and older**

Health status: **Men and women recently diagnosed with a cancer of favorable prognosis (localized and regional staged female breast, and**

prostate cancers; localized colon & rectum, uterine cervix & corpus, kidney/renal pelvis, non-Hodgkin lymphoma, oral cavity/pharynx, and esophagus cancers; and in situ bladder cancer); and have no medical conditions that would preclude gardening or the consumption of a diet high in fruits and vegetables (e.g., pharmacologic doses of warfarin) – see inclusion/exclusion criteria following page.

*Note. If data from prior studies indicate differences between the genders or among racial/ethnic groups in the proposed research or if there are no data to support or to negate such differences, Phase 3 clinical trials will be required to include sufficient and appropriate entry of gender and racial/ethnic subgroups so that trends detected in the affected subgroups can be analyzed. If ethnic, racial, and gender estimates are not included in the protocol, a clear rationale must be provided for exclusion of this information. If prior evidence indicates that the results will not show gender or racial differences, researchers are not required to use gender or race/ethnicity as selection criteria for study participants. They are, however, encouraged to include these groups. See Section II. Policy of the NIH POLICY AND GUIDELINES ON THE INCLUSION OF WOMEN AND MINORITIES AS SUBJECTS IN CLINICAL RESEARCH – Amended, October, 2001) for further details.*

c. From what population(s) will the participants be derived?

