**Participants will be recruited into 8 cohorts [From Cohort 1 (Start in Year 1) to Cohort 8 (Start in Year 3)] to achieve our accrual goal of 426 participants. Each cohort will be comprised of 52-54 participants. Participants will then be randomized to 1-of-2 study arms: 1) an intervention group that receives an immediate 1-year mentored vegetable gardening intervention in the first year (26-27 participants), or 2) a wait-listed group that receives a delayed 1-year mentored vegetable gardening intervention in the second year (26-27 participants). All participants will be on study for two years. Participants will be block randomized within 2 strata defined by the number of physical function limitations as assessed by the SF36-PFSS (2 vs.  $\geq 3$ ). Participants would be assigned with equal allocation either group A or group B below:**

**Group A:** Participants assigned to this group, would be paired immediately with a Master Gardener from the Cooperative Extension in their county of residence. They also would be given supplies (soil, plants, seeds, and fertilizer) to support either 4 earth boxes (which can be used to garden on balconies, patios or decks) or 1 raised bed garden. These supplies will be provided free of charge. Master Gardeners will make monthly visits to guide participants in setting-up the garden, maintaining it, and replanting it season-to-season. Every month, Master Gardeners also will contact survivors by telephone or email (based on survivor preference) to check-in on garden status and to field questions or problems.

**Group B:** Participants assigned to this group, would receive the exact same program as Group A (see above), but would receive it AFTER a waiting period of one year. During the wait period, UAB study staff will send participants quarterly holiday postcards reminding them about the study and letting them know that we are looking forward to delivering the program to them in the upcoming year. These postcards will encourage wait-listed participants to contact us if their address or health status changes. These postcards are planned for New Year's, St Patrick's Day, 4th of July and Thanksgiving.

- e. Indicate which, if any, of the special populations listed below will be involved in the protocol. Include the Special Populations Review Form (SPRF) if indicated.
- ☐ Pregnant Women: Attach [SPRF—Pregnant Women, Fetuses, Neonates/Nonviable Neonates](#)

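### Section 19.a assumes independent adverse events within each arm, although one participant can report several; if all events are counted, rate intervals will be too narrow and arm comparisons anti-conservative

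*Protocol*

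**What the plan says.** Section 19.a describes how adverse events are gathered and used.

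- Routine asking: "All patients will be asked if and when they suffered adverse events during bi-monthly telephone contact with study staff".
- Spontaneous reports: participants "will be encouraged to report an event at any time during follow-up", and a toll-free line is provided.
- Exposure: "Thus, at any given time, patients will have varying follow-up times".
- Use: data from "these phone calls will be included in the analyses along with data generated by the follow-up surveys", after a check for duplicates and cleaning.
- Assumption: "Within each arm, we assume independence of events".

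On design, Section 15.a gives a total of "426 older cancer survivors". Section 15.d says "Participants would be assigned with equal allocation" and "All participants will be on study for two years", with the wait-list arm receiving the gardening program in the second year. Section 17 lists adverse events among the process data under its first purpose. Section 19.c answers multiple serious events by consultation.

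The protocol states no adverse-event rate, interval, between-arm safety test or significance level.

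**The concern.** The sentence is an explicit statistical assumption about data that the protocol says will be analysed, so it is more than a detail left to the SAP. It is made about events, not about people.

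The protocol gives reason to expect that people differ in how prone they are to events. Entry requires age 65 or older and at least two physical function limitations (Section 15.c). Randomization is stratified by two versus three or more limitations (Section 15.d). The number and severity of chronic conditions are measured (Section 16.a). If frailer participants have more events, events from one person are positively correlated, and the count in an arm varies more than it would under independence. Removing duplicates stops one event being counted twice. It does nothing about one person having several different events.

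At stake is how any safety summary is read. A chance cluster of events in a few frail people in one arm could be taken for a harm, or a benefit, of gardening.

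**Working it through.** The protocol states no figure on this point, so there is none to reproduce. The check asks how far an analysis that counts all events as independent would be off.

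**Inputs from the protocol.** Total 426, equal allocation, so 426/2 = 213 per arm. The wait-list arm starts the program in year 2, so the period taken is year 1.

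**Assumed inputs, not in the protocol.** Mean events per participant-year μ from 0.05 to 1. Between-person variance φ of the relative event rate from 0.5 to 2, with φ = 0 meaning that independence holds. Event counts are Poisson given the person, with gamma-distributed rates between people. Everyone is followed for the full year.

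**Formulas.**

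- Variance of an arm's event rate under independence: μ/213.
- True variance: μ(1 + μφ)/213.
- Variance ratio: 1 + μφ.
- True interval half-width divided by the naive one: √(1 + μφ).
- True two-sided error of a nominal 5% test: 2[1 − Φ(1.96/√(1 + μφ))]. Both arms carry the same factor, so it applies to the difference as well.

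**One case in full, μ = 0.5 and φ = 1.**

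- Naive standard error: √(0.5/213) = 0.0485, so the half-width is 1.96 × 0.0485 = 0.095 events per person-year.
- Variance ratio: 1 + 0.5 × 1 = 1.5, and √1.5 = 1.22, so the true half-width is 0.095 × 1.22 = 0.116.
- True error: 1.96/1.22 = 1.60, and 2[1 − Φ(1.60)] = 11.0%.

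**Range for φ from 0.5 to 2.**

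| μ per person-year | Variance ratio | Half-width ratio | True error of nominal 5% test |
|---|---|---|---|
| 0.05 | 1.025 to 1.10 | 1.01 to 1.05 | 5.3% to 6.2% |
| 0.2 | 1.10 to 1.40 | 1.05 to 1.18 | 6.2% to 9.8% |
| 0.5 | 1.25 to 2.00 | 1.12 to 1.41 | 8.0% to 16.6% |
| 1 | 1.50 to 3.00 | 1.22 to 1.73 | 11.0% to 25.8% |

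A simulation with 213 per arm and 10,000 runs per setting agrees within about 1 percentage point. It gives about 5% when φ = 0, as it should. At μ = 1, a naive 95% interval for one arm's rate covers the truth in 88.8% of runs (φ = 0.5) down to 73.9% (φ = 2).

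**After correction.** Over the same settings, a variance computed from participant totals gives a simulated error of 4.7% to 5.4%. Comparing the proportions of participants with any event gives 4.5% to 5.3%.

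**The case against.** The strongest reply is that the affected analysis is not in the document. With no rate, interval, test or significance level for adverse events, no decision in the protocol depends on a standard error, and Section 19.c relies on judgement. This stands, and it makes the consequence conditional. A reader might infer that the trial's safety intervals are already too narrow and its false signals already inflated. The protocol does not support that, because it never says that all events will be counted in a rate or tested between arms.

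Second, the sentence may have been meant for participants. It follows wording about whether and when events occurred and about unequal follow-up, which fits a time-to-first-event analysis. The call-in line is described as being for events that would preclude participation, and these should seldom recur in one person. This reading is possible, and under it the problem disappears. But the text says events, and nothing limits the analysis to first events or to participants with any event. If participants were meant, the sentence still needs correcting.

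Third, events may be rare. Section 19.a calls the risks minimal, and Section 14 reports few adverse events in two earlier home-based trials. For rare serious events the effect is indeed close to nil. On the other hand, Section 19.a records every health occurrence, which could be frequent. Both ends belong in the range.

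Fourth, asking repeatedly does not make events recur. This is correct: the contact schedule shows that several events per person can be captured, not that there will be many.

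Finally, the choice of model is usually left to the SAP, which was not available here. That covers the method, but not a wrong assumption stated in the protocol.

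**Conclusion.** The point holds in conditional form. As written, the assumption is wrong for any analysis that counts all events, provided participants differ in their tendency to have events, which the protocol's own entry criteria and strata make plausible. The direction is then clear: intervals too narrow and comparisons anti-conservative.

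The size is uncertain, because the event rate and the between-person variance are both assumed. It runs from negligible for rare events to a true error of about one in four at one event per person-year with strong heterogeneity. A reader might take the upper figures as the expected inflation, but the protocol gives nothing to place the trial within the range. Confidence is high in the premise and direction and low in the size. The correction is worth making because it is cheap and the sentence as it stands points to the wrong variance.

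**What to change.** Replace the sentence in Section 19.a with a statement that participants are assumed independent and that events from the same participant may be correlated. Then state that each arm's report will give:

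1. the number and proportion of participants with at least one event;
2. events per person-year, compared by negative binomial regression, or by Poisson regression with participant-level robust variance, with log follow-up time as offset.

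Separately from the independence question, state that the randomized between-arm contrast for adverse events is year 1, because the wait-list arm receives the program in year 2. Year 2 can be described by arm.

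The cost is a few lines of text and slightly wider intervals for event rates. No further data are needed, provided each event is stored with the participant's study number and date.

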We will include individuals who: (1) are diagnosed with a loco-regionally staged cancer associated with an 80% or greater 5-year survival rate (localized and regional staged female breast, and prostate cancers; localized colon & rectum, uterine cervix & corpus, kidney/renal pelvis, non-Hodgkin lymphoma, oral cavity/pharynx, and esophagus cancers; and in situ bladder cancer); (2) reside in the state of Alabama; (3) completed primary curative cancer treatments, i.e., surgery, chemotherapy or radiation therapy; (4) are at least 65 years of age; (5) are at higher risk of functional decline ( $\geq 2$  physical function (PF) limitations as defined by the SF36 PF subscale); (6) currently eat less than 5 servings of fruits and vegetables (F/V)/ day; (7) exercise less than 150 minutes/ week; (8) speak and write in English (some of our scales are not validated in other populations/languages); and (9) are willing to be randomized to either study arm and participate in the follow-up assessments. We will exclude individuals who: (1) are not competent due to mental health or other very serious comorbid conditions (e.g., severe orthopedic conditions or scheduled for a hip or knee replacement with 6 months, paralysis, unstable angina or who have experienced a myocardial infarction, congestive heart failure or pulmonary conditions that require hospitalization or oxygen within 6 months, stroke, degenerative neurological conditions); (2) have any medical condition substantially limiting moderate physical activity; (3) currently taking pharmacologic

doses of warfarin (does not include doses taken to maintain a port); (4) do not reside in a location that can accommodate 4 or more Earthboxes or 1-raised bed (4'x 8'), and that get at least 4 hours of sun a day; (5) do not have running water; (6) have recent experience with vegetable gardening, e.g. planted a vegetable garden within the past year; or (7) have a history of lymphedema flares, axillary node dissection of 10 or more lymph nodes per side.

- d. If participants will comprise more than one group or stratification, describe each group (e.g., treatment/intervention, placebo, controls, sham treatment) **and** provide the number of participants anticipated in each group.

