**17. Describe the potential benefits of the research.**

The benefit to society is reasonably high since the proposed intervention may help improve lifestyle behaviors that could potentially impact progressive disease and co-morbidities in cancer survivors. Thus, this project serves many purposes: (1) To explore the feasibility and acceptability of a mentored vegetable gardening intervention. This aim will be accomplished by collecting detailed process data, which will allow the assessment of accrual, retention, adherence/fidelity, and adverse events; (2) To quantify (mean change scores and precision estimates) and compare between-arm differences in physical function as measured by the Short Form 36 Physical Function Subscale (SF36-PFSS); (3) To explore participant factors associated with program efficacy, e.g., gender, and comorbidity; and (4) To obtain means and precision estimates and explore between-arm differences on pre-post changes in secondary endpoints: (a) physical performance tests (Short Physical Performance Battery (SPPB) & Senior Fitness Tests), (b) biomarkers of physical function and healthful aging (e.g. IL-6, D-dimer, & telomerase), (c) F&V intake and diet quality (DQ), (d) accelerometer measured PA, (e) BMI, (f) health-related quality of life (HRQoL), and (g) reassurance of worth.

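### Item 19.b does not separate stopping the gardening from leaving the assessments, so 1-year function values may be lost after serious events, possibly unequally by arm

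*Protocol*

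**What the plan says.** Item 19.b (Precautions/Minimization of Risks) has the project manager report serious events to the principal investigator, who consults a co-investigator on what to do. It then says: "If deemed necessary, participants will be removed from the study to ensure their safety". A serious event includes one that "results in overnight hospitalization, cancer or a physical or cardiac event serious enough to require medical attention".

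Item 19.a also speaks only of taking part in the study as a whole: "study participants will be encouraged to call-in on a toll-free number to report any adverse events that would preclude their participation in the study". Adverse events are sought in both arms: "All patients will be asked if and when they suffered adverse events during bi-monthly telephone contact with study staff". On use of the reports, it says that data from "these phone calls will be included in the analyses along with data generated by the follow-up surveys".

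Four other parts of the protocol bear on this:

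- **Item 15.c.** Inclusion criterion 9 requires that entrants "are willing to be randomized to either study arm and participate in the follow-up assessments".
- **Item 15.d.** Everyone is to be on study for two years. Group A gardens in the first year. Group B receives the same programme after a one-year wait.
- **Item 16.e.** The SF36 physical function subscale and the performance tests are done three times: at baseline, 1 year and 2 years. The mailed 6- and 18-month contacts carry the activity (CHAMPS) and diet (EATS) questionnaires, not the function subscale.
- **Item 17.** The SF36 physical function subscale is the measure on which between-arm differences in physical function are to be compared.

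**The concern.** Stopping an activity for safety and ceasing to measure a participant are different decisions, and the protocol has words only for leaving the study. Followed as written, a removal in the first year also ends the schedule that would have supplied that person's 1-year function value.

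The loss would be informative. Hospital admissions, new cancers and cardiac or physical events plausibly lower physical function, so the missing values would tend to be the poorer ones. It could also depend on arm, because in year 1 only Group A has gardening to be stopped. Year 1 is also the period in which the wait-list design contrasts gardening with no gardening. Follow-up of harms could be cut short for the same people.

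This is a rule of conduct. An analysis plan can say how missing values are handled, but it cannot recover values that were never collected.

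**Working it through.** The protocol states no removal rate, SD, alpha, power or effect size, so there is no figure of its own to reproduce. What follows is a sensitivity calculation.

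**Inputs from the protocol.** 426 participants with equal allocation (Item 15.d) give 426 / 2 = 213 per arm. There is one function value per participant in year 1 (Item 16.e).

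**Assumed inputs.** pA and pB are the shares removed before year 1 in Groups A and B and not assessed again. They are varied from 0% to 10%. g is how many SD worse the removed participants' 1-year function is than that of those who stay in the same arm. It is set at 0.5 and 1.0. The test is two-sided at 0.05 and uses observed values only.

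**Bias.** If those who stay have mean m, the whole arm has mean m − p·g, so the observed mean is too high by p·g. The between-arm bias is

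bias = (pA − pB) × g.

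**Standard error, in SD units.** SE = √[1/(213(1 − pA)) + 1/(213(1 − pB))]. With no removals this is √(2/213) = 0.097.

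**Two-sided error under no true effect.** P(Z > 1.96 − bias/SE) + P(Z < −1.96 − bias/SE).

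Example, 10% in A, 0% in B, g = 1.0:

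- bias = 0.10 × 1.0 = 0.10
- SE = √(1/191.7 + 1/213) = 0.0996, so bias/SE = 1.00
- error = 0.1697 + 0.0015 = 0.171

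| Removed A / B | Bias, g = 0.5 | Bias, g = 1.0 | Error, g = 0.5 | Error, g = 1.0 |
|---|---|---|---|---|
| 2% / 2% | 0 | 0 | 5.0% | 5.0% |
| 5% / 5% | 0 | 0 | 5.0% | 5.0% |
| 2% / 0% | +0.010 | +0.020 | 5.1% | 5.5% |
| 5% / 2% | +0.015 | +0.030 | 5.3% | 6.1% |
| 5% / 0% | +0.025 | +0.050 | 5.8% | 8.0% |
| 10% / 5% | +0.025 | +0.050 | 5.7% | 7.9% |
| 10% / 0% | +0.050 | +0.100 | 7.9% | 17.1% |
| 2% / 5% | −0.015 | −0.030 | 5.3% | 6.1% |

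A positive bias favours the intervention. For scale, at an assumed 80% power the detectable difference with 213 per arm is (1.96 + 0.84) × 0.097 = 0.27 SD.

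**After the change.** If the removed participants are still assessed at year 1, this bias is zero in every row and the error returns to 5%.

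**The case against.** A reader might infer that everyone with a hazard is to be taken out, that their outcomes are deleted, and that the function benefit will therefore be overstated. The documents do not support that.

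- **Removal is conditional.** It is one possible result of a consultation. The serious-event list sets off reporting and consultation. It is not a list of removal triggers.
- **Nothing is deleted.** No text discards collected data or excludes removed participants from analysis, and adverse-event reports are explicitly kept. Criterion 9 and the two-year statement in Item 15.d point towards continued follow-up.
- **The phrase comes from the form.** The question being answered asks the applicant to "describe (i) the criteria that will be used to decide whether that participant should be removed from the study". Repeating its words is weak evidence of a deliberate choice to end outcome collection.
- **Imbalance is not shown.** Adverse events are asked about in both arms, and the serious-event definition is not confined to gardening. Older participants with functional limitations can have such events in either group. Item 14 reports few adverse events and low attrition in the team's two earlier home-based trials, which lends no support to removal rates as high as 10%.
- **Other documents may help.** The analysis plan and consent form are not at hand. Missing-data handling and analysis by assigned arm may be settled there and are not part of this point.

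All of this stands against the stronger reading. It leaves the gap in Item 19.b: the one rule that the protocol states is removal from the study, and nothing in it says that assessment continues. The function schedule offers no earlier post-baseline value to fall back on.

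**Conclusion.** The point holds as a defect in a stated conduct rule. It does not show a bias in favour of the intervention. Item 19.b leaves open whether a participant stopped from gardening is still measured. Read literally, it costs the 1-year function value of anyone removed before that visit, for a reason plausibly tied to function.

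A lean towards the intervention is plausible, because only Group A gardens in year 1, but it is not certain. Under the assumed rates the bias is about 0.01 to 0.10 SD when Group A loses more, zero when losses are equal, and −0.015 to −0.03 SD in the case where Group B loses more (2% against 5%). It is small unless removals are both frequent and one-sided. The 0.10 SD end needs 10% removed in Group A, none in Group B and a full 1 SD deficit. The figures also assume that removed participants are not assessed again and that the comparison rests on observed values alone. The case for the change is that it is cheap and that the lost data cannot be recovered later.

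**What to change.** Add to Item 19.b, in substance:

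*A participant who is stopped from gardening for safety will still be asked, if they agree, to complete the remaining planned questionnaires (by mail if needed) and any home assessments that the investigators judge safe. Adverse-event contact will continue.*

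Make the matching passage in Item 19.a distinguish events that prevent gardening from events that prevent assessment. Who stops gardening, and when, stays as the plan has it, and so does the investigators' discretion to take someone out of the study for safety.

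The cost is a sentence or two of text and some follow-up effort for a few participants, within visits, mailings and calls already planned. Criterion 9 already asks entrants to be willing to take part in the follow-up assessments. The consent form should be checked for agreement with the new wording.
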